## Abstract

**Background:**

Among glioma patients, depression is estimated to be more prevalent than in both the general population and the cancer patient population. This can have negative consequences for both patients and their primary informal caregivers (e.g., a spouse, family member or close friend). At present, there is no evidence from randomized controlled trials for the effectiveness of psychological treatment for depression in glioma patients. Furthermore, the possibility of delivering mental health care through the internet has not yet been explored in this population. Therefore, a randomized controlled trial is warranted to evaluate the effects of an internet-based, guided self-help intervention for depressive symptoms in glioma patients.

**Methods/design:**

The intervention is based on problem-solving therapy. An existing 5-week course is adapted for use by adult glioma patients with mild to moderate depressive symptoms (Center for Epidemiology Studies Depression Scale score ≥12). Sample size calculations yield 126 glioma patients to be included, who are randomly assigned to either the intervention group or a waiting list control group. In addition, we aim to include 63 patients with haematological cancer in a non-central nervous system malignancy control group. Assessments take place at baseline, after 6 and 12 weeks, and after 6 and 12 months. Primary outcome measure is the change in depressive symptoms. Secondary outcome measures include health-related quality of life, fatigue, costs and patient satisfaction. In addition, all patients are asked to assign a primary informal caregiver, who does not participate in the intervention but who is asked to complete similar assessments. Their mood, health-related quality of life and fatigue is evaluated as well.

**Discussion:**

This is the first study to evaluate the effects of problem-solving therapy delivered through the internet as treatment for depressive symptoms in glioma patients. If proven effective, this treatment will contribute to the mental health care of glioma patients in clinical practice.

**Trial registration:**

Netherlands Trial Register NTR3223

## Background

Patients with gliomas, primary brain tumors originating from glial tissue, are not only faced with the diagnosis of a life-threatening disease, but also with various neurological symptoms [1,2]. Glioma patients often suffer from headaches [3-5], cognitive deficits, paresis, visual-perceptual deficits, sensory loss, and seizures [1]. In addition, depression is common in glioma patients. During the first 8 months following the diagnosis, 15 to 20% of glioma patients become clinically depressed [6,7]. Longitudinal studies show that the prevalence of depression among these patients keeps increasing up to one year after surgery [8]. Surprisingly, glioma patients not only seem to be at increased risk compared with the general population (12-month prevalence 6.6%), but also compared with other cancer patient populations [9,10]. This may affect not only patients, but also their direct environment, including their spouses, family members, and close friends. In fact, glioma patients’ neuropsychiatric status, including depressive symptoms, was found to influence the presence of depressive symptoms in significant others [11]. These mental health issues can contribute significantly to a decrease in significant others’ health-related quality of life (HRQOL) [12,13].

The precise cause of depression in glioma patients remains unclear. A number of mechanisms, including tumor location, elevated intracranial pressure, and biochemical changes may contribute to the development of depression [14]. Evidently, the patient’s emotional reactions to the diagnosis can contribute. Patients can experience shock and disbelief, dysphoria, despair, anger and anxiety, and intrusive thoughts about their diagnosis [15]. These issues may cause an adjustment disorder to the situation, which if persistent, can become a major depressive episode [16]. However, evidence for this theory is inconclusive as awareness of the prognosis is not always associated with mood disorders [17]. Moreover, these mechanisms occur in other cancer patient populations as well, which only emphasizes the unexpectedly high prevalence of depression among glioma patients, specifically.

While the etiology of this problem is not fully known, it is clear that the above mentioned contributing factors may impede the diagnosis of depression in glioma patients [18]. For example, the mood problems can be interpreted by treating physicians as ‘understandable’ considering the circumstances, and this may complicate communication about these symptoms [19]. The depression is then less likely to be recognized, which can lead to an underdiagnosis, and subsequently to an undertreatment, of depression [20]. This process can have serious negative consequences for glioma patients as in this population, depression has been associated with increased morbidity and even with poorer survival [21,22]. Moreover, depression is the most important independent predictor of HRQOL in patients with brain tumors [23].

If this potentially treatable condition is recognized, the treatment usually consists of the combination of antidepressants and intensive psychological treatment, such as cognitive behavioral therapy (CBT) [24,25]. Both pharmacological and psychological treatment can encounter problems in glioma patients specifically. Glioma patients often take multiple medications concurrently, which increases the risk for drug interactions and may lead to a reluctance to try antidepressants. For example, one study shows that only 60% of patients in whom the treating physician recognized depression, actually received antidepressants [26], and it is unclear if the remaining 40% of depressed patients received an alternative treatment such as psychotherapy. Treatment with psychotherapy can encounter problems as well, as psychotherapy usually requires good cognitive functioning in order for a patient to benefit most while approximately 80% of brain tumor patients experience cognitive deficits to some degree [1]. Therefore, while treatment for depression has been shown effective in both the general population [27,28] and in cancer patients [29], it remains to be seen if either antidepressants or psychotherapy are equally effective in glioma patients.

Problem-solving therapy (PST), a form of CBT, may prove helpful in alleviating depressive symptoms especially in this patient population, as it is a brief and practical approach. Depression is linked with stressful life events, and when depressed, patients may be less able to actively cope with these stress inducing factors. In PST, it is assumed that depressive symptoms are caused by everyday problems that can be resolved with problem-solving techniques. Resolution of problems then leads to a reduction in depressive symptoms. By teaching more adequate coping strategies, and aiding in the acceptance of problems that cannot be solved [30], PST can prove effective [31,32]. Indeed, it has been suggested as the preferred treatment in depressive patients with somatic disease [33].

During their disease trajectory, glioma patients frequently have to visit the hospital. In a subset of patients who suffer from neurological sequelae that affect their physical functioning and mobility (e.g. paresis, paralysis, epilepsy, fatigue), face-to-face treatment for depression may lead to additional burden. Alternative ways of delivering PST, such as through the internet, may therefore become more appealing. This may especially be the case in the Netherlands, where in 2013, approximately 95% of all households has internet access [34]. Internet-based psychological interventions, including PST, have already been found to be equally effective as face-to-face treatment [27,35]. These internet-based programs make use of self-help, where patients work through a standardized psychological treatment independently, sometimes guided by a coach. This way, the interventions are thought to pose low thresholds for participation, as it is more anonymous, easily accessible as patients can work on the programs at a time of their choosing, and cost-effective as only minimal involvement of health-care professionals is necessary. As of yet, there is no scientific evidence from randomized controlled trials available for the effectiveness of psychotherapy, whether internet-based or face-to-face, in glioma patients [36]. Therefore, we presently present the design of a randomized, controlled trial aimed at alleviating depressive symptoms in glioma patients using an internet-based guided self-help course. A secondary aim is to evaluate the effect of the intervention on HRQOL of both patients and their significant others.

## Methods/design

### Design

This study is a randomized controlled trial evaluating the effects of an internet-based guided self-help course for depressive symptoms in glioma patients. We compare a group of patients who receive the intervention with a three month waiting list control group and a non-central nervous system malignancy control group. The intervention, which takes approximately 5 weeks to complete, is aimed at patients with mild to moderate depressive symptoms.

Assessments include self-reported outcomes completed online. The assessments are scheduled at baseline (T0), after completion of the online course (approximately 6 weeks after baseline; T1), 12 weeks after baseline (T2), and 12 months after baseline, see Figure 1. Those in the waiting list control group receive the same assessments, but are also assessed after completion of the online course (T3; approximately 6 weeks after T2), and 12 weeks thereafter (T4). Furthermore, patients with a high-grade malignancy undergo an additional assessment at 6 months after baseline (T3 or T5), as is also depicted in Figure 1. This study is performed in accordance with the Declaration of Helsinki.

**Figure 1 F1:**
[figure not shown]
Participant flow.

This study is approved by the institutional review board of the VU University Medical Center (IRB00002991). Due to the internet-based nature of the intervention and the assessments, this approval is deemed sufficient for nation-wide recruitment.

### Study population

Adult (>18 years of age) WHO grade II, III or IV glioma patients with mild to moderate depressive symptoms (Center for Epidemiological Studies Depression Scale [37] (CES-D) score ≥12) are invited to participate. After screening, patients scoring above 16, the usual cut-off score for depression on the CES-D, subsequently receive the full study information. Those scoring between 12 and 16 are informed of their relatively low score and are given the option to receive the full study information or not.

For the non-central nervous system oncology control group, adult (>18 years of age) patients with non-Hodgkin lymphoma (NHL), chronic lymphatic leukaemia (CLL), multiple myeloma (MM), or a myelodysplastic syndrome (MDS) who have mild to moderate depressive symptoms (CES-D score ≥12) are invited to participate. Here, too, those patients scoring between 12 and 16 on the CES-D at the time of screening are informed of their relatively low score and they are asked if they want to receive full information of the study or not.

Although not a strict requirement for participation, all patients are additionally asked to invite an informal caregiver to participate in the study. This refers to a significant other who provides the majority of mental and physical support to the patient. These informal caregivers do not participate in the intervention but are asked to complete the same assessments at the same time points concerning their own mood, HRQOL, fatigue, etc.

Potential participants are excluded if they have no access to the internet and/or no email address, if they have insufficient proficiency of the Dutch language, and if they express suicidal intent. Suicidal intent is screened for with the Beck Scale for Suicide Ideation (BSS) [38]. If patients have a score higher than 0 on the BSS, a board certified psychologist (MK) conducts an interview through telephone to assess the severity of symptoms. If a patient is excluded due to suicidal intent, the general practitioner is always contacted to assure proper referral to health care professionals.

### Recruitment and inclusion procedure

Patients are recruited through advertisements and news items on websites frequently visited by glioma patients and haematological patients. Patient associations are asked for help in spreading study information through their websites, newsletters and meetings. Treating physicians and nurse practitioners throughout the Netherlands collaborate in this study by providing information brochures to their patients. These professionals are contacted through the intermediary of the Dutch Society for Neuro-Oncology and the Dutch Neurology Association, as well as through the authors’ personal networks.

The advertisements, news items and information brochures contain a link to a website with an online screening procedure. If interested, patients complete this online questionnaire that contains questions on basic demographic information (age, gender, level of education), contact information, and the BSS and CES-D. On this website, it is explained that by completing the questionnaire, patients give permission to contact their general practitioner if the researchers deem this necessary. Furthermore, they are made aware that the personal information they provide will only be used if they later decide to take part in the study and sign informed consent forms.

Eligible patients receive an information letter. Within a week the study coordinator ([name]) contacts the eligible patients by telephone to answer possible questions. Subsequently, they are asked to sign the informed consent form they received with the information letter. They are also asked to sign a form enabling the researchers to request information on the patient’s disease and treatment at their treating hospital. Figure 2 illustrates this recruitment procedure. After informed consent is obtained, both the general practitioner and the treating physician are informed about the patient’s intent to participate in the trial.

**Figure 2 F2:**
[figure not shown]
Recruitment procedure.

### Randomization

Glioma patients are randomly assigned to either the intervention group or the waiting list control group after completion of the baseline assessment (T0). An adaptive simple randomization technique is employed to minimize the chance of imbalanced group sizes.

### Intervention

The internet-based guided self-help intervention is based on the principles of problem solving therapy. The original intervention, ‘Everything under control’ (“*Alles onder controle*”) has been shown to have significant positive effects on depression, anxiety and stress/burnout in a randomized controlled trial with 215 adults from the general population [39]. With small changes, this online intervention is adapted for use by glioma patients and patients with haematological malignancies. Modifications concern additional information about the specific diseases and their treatment, and the psychological impact on everyday life. Examples of participants’ assignments are made disease-specific.

The intervention consists of 5 modules with text and exercises. Patients are asked to complete one module a week and spend a minimum of two hours a week on their exercises. During the intervention, patients describe what they feel is important in their lives, make a list of their problems and concerns, and divide these into three categories: 1) unimportant problems (problems that are not related to what is important in their life), 2) important and solvable, and 3) important but unsolvable. For each of these problems the patient makes a plan on how to cope with this, guided by methods explained in the modules. The participants receive feedback on the exercises from a personal coach within three working days after completion of the assignment. The coach is not a therapist, but only supports the patient in working through the intervention. Participants can always contact their coach for additional support through the website. The coaching is provided by one of the researchers ([name]), by trained and supervised students in the final phase of a Master’s program in Psychology or by specialists from Prezens. In collaboration with the VU University medical center, Prezens provides psychological care and support.

The glioma patients in the waiting list control group are offered the same intervention after completion of the 12 weeks follow-up (T2).

### Outcome measures

Self-report measures of depressive symptoms, HRQOL, fatigue, costs and patient satisfaction are presented online in a fixed order. Patients are allowed to return to any of the measures for review or changes during an assessment.

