#### Patient satisfaction

During the post-intervention assessment (T1 or T3), the patients’ experience with the online course is evaluated. A short study-specific questionnaire evaluating the usability, readability, course content, and self-perceived usefulness of both the online course and the feedback provided by the coach is presented along the other questionnaires. Room for remarks is provided as well.

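### At T1 only one of the two randomised arms rates the course and coach in the same online assessment as the CES-D, while the CES-D answers can still be changed

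*Protocol article*

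**What the plan says.** All references are to the protocol article.

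- **Outcome measures:** "Self-report measures of depressive symptoms, HRQOL, fatigue, costs and patient satisfaction are presented online in a fixed order". The next sentence reads: "Patients are allowed to return to any of the measures for review or changes during an assessment". It makes no exception for the CES-D.
- **Patient satisfaction:** a study-specific questionnaire is given at the post-course assessment, T1 or T3. It covers usability, readability, content and "self-perceived usefulness of both the online course and the feedback provided by the coach", and it "is presented along the other questionnaires".
- **Intervention:** "The glioma patients in the waiting list control group are offered the same intervention after completion of the 12 weeks follow-up (T2"). On coaching: "The coaching is provided by one of the researchers", by supervised psychology students, or by specialists of an outside care provider.
- **Design:** outcomes are self-reported online. T1 falls about 6 weeks and T2 12 weeks after baseline. The waiting list has its own post-course assessment (T3) about 6 weeks after T2.
- **Primary outcome measure:** change in CES-D. No single primary time point is named.

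**The concern.** A randomised comparison of a self-reported score relies on both arms being measured in the same way. Here patients cannot be blinded, so the measurement procedure is one of the few protections left.

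A fixed order with the CES-D first would keep the usefulness items from influencing the CES-D. The permission to reopen any measure removes that protection. An intervention patient at T1 can be asked how useful the course and the coach were, and then return to the depression items in the same assessment. A waiting-list patient at T1 may also reopen the CES-D, but has had no course and no coach to rate. In some cases the coach being rated is a member of the study team, which could add some pressure on the answers.

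At stake is whether part of a T1 difference in CES-D reflects a difference in measurement and not in depressive symptoms.

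**Working it through.** **1. The sections side by side, for the two randomised arms**

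| Assessment | Intervention arm: satisfaction items due? | Waiting list: satisfaction items due? | CES-D open to change within the assessment? |
|---|---|---|---|
| T0 | no | no | both arms |
| T1 (about 6 weeks) | **yes** | **no** (no course yet) | both arms |
| T2 (12 weeks) | no | no | both arms |
| T3 (about 6 weeks after T2) | not applicable | yes (after own course) | – |

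The satisfaction rows follow from Patient satisfaction (T1 or T3) and Intervention (waiting-list course after T2). The last column follows from Outcome measures. The arms differ at T1 only, and they differ in the satisfaction items, not in the freedom to revise. By T3 the waiting list has had the course, so T1 and T2 are the time points at which course is compared with no course.

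**2. The plan's own figures**

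The plan gives no figure on this point. To express a shift on the plan's scale I use its d of 0.50 and 50 patients per condition (Sample size). The 50 reproduces with a one-sided 5% test: 2 × (1.645 + 0.842)² / 0.50² = 49.5, rounded up to 50. A two-sided test gives 63. That is a separate matter, and nothing here depends on it.

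**3. What a shift would do, if there were one (assumption)**

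Let b be a mean shift in one arm's T1 CES-D, in SD units, that comes from reporting alone. With 50 per arm the standard error of d is about √(2/50) = 0.20. With no true effect, the two-sided 5% rejection rate is 1 − Φ(1.96 − b/0.20) + Φ(−1.96 − b/0.20).

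| Assumed b | Share of planned d (b/0.50) | b/0.20 | Rejection rate with no true effect |
|---|---|---|---|
| 0.05 | 10% | 0.25 | 5.7% |
| 0.10 | 20% | 0.50 | 7.9% |
| 0.20 | 40% | 1.00 | 17.0% |

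The formula is symmetric in the sign of b. A shift against the intervention would instead mask benefit: with b = 0.10, a true d of 0.50 would appear as 0.40.

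**4. What such a shift would need**

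The article gives no CES-D standard deviation. If it were 8 to 10 points, a mean shift of 1 point would be 1/10 = 0.10 to 1/8 = 0.125 SD. If only some patients revise, each must change a good deal to move the arm mean by 1 point: 10 points each if 10% revise (0.10 × 10 = 1), or 20 points each if 5% revise (0.05 × 20 = 1), on a scale of 0 to 60. A shift of that size is possible but would take substantial revision.

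**The case against.** The case on the other side is strong on several points.

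- **The listed order helps.** Depressive symptoms are named first and satisfaction last. The sequence is not spelled out, but this is the natural reading. If so, the first CES-D answer cannot be primed, and only going back after the last questionnaire remains as a route. This stands, and it narrows the risk.
- **Nothing shows that patients revise, or which way.** The satisfaction items can draw criticism as well as praise. A reader might infer that scores are pushed towards improvement; the documents do not support a direction.
- **Correction is useful in this population.** The Background section says that roughly four in five brain tumour patients have some cognitive deficit, so letting them fix mistakes is defensible. This stands, and it argues against locking every questionnaire one by one.
- **Coaches are not only researchers**, and the Discussion section says the questionnaires are kept apart from the course website. Both stand. Neither separates the satisfaction items from the CES-D.
- **Unblinded self-report comes with a waiting-list design.** True, but placing a one-arm usefulness rating beside an open primary outcome does not.
- **Screen settings belong in the full protocol.** That would answer a complaint about missing detail. Here the article states the permission to reopen any measure outright.

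Stronger readings are tempting. A reader might infer that only the intervention arm may change answers; the rule covers all patients. A reader might infer that controls never meet the items; the waiting list does at T3, and the haematological group, for whom the course is also adapted, may rate it too. A reader might infer that the trial has no way round the problem; T2 is a randomised comparison in which neither arm is due the items.

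**Conclusion.** The point holds in a limited form. At T1, of the two randomised glioma arms, only the intervention arm rates the course and coach within the assessment that contains the CES-D, and the stated rule leaves the CES-D open to change. This is an avoidable difference in how an unblinded, self-reported primary outcome is measured.

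The effect on the trial's main result is uncertain. It is confined to T1, and because no primary time point is named, it depends on how much weight T1 carries. The size and direction of any shift cannot be derived from the documents; the figures in the tables show sensitivity under assumed shifts and are not estimates. It would go too far to say that the primary result is biased. This is a cheap improvement, not a fault that undermines the design.

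**What to change.** In Outcome measures, state that the CES-D is presented first and that patients may review and correct answers across all outcome questionnaires until they submit them together. In Patient satisfaction, state that the satisfaction questionnaire opens only after all outcome questionnaires of that assessment have been submitted and closed. Apply both rules in all groups.

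The cost is a setting in the questionnaire software and two sentences. The downside is that outcome answers cannot be corrected once the satisfaction items open. The article says the trial is already recruiting, so the date of the switch should be recorded; assessments before and after it can then be told apart.
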